### Intervention

ADCompanion strengthens the holistic care of patients with AD in underserved regions through location-independent access to the following interdisciplinary care components.

#### Online Access to Qualified Training Content and Standardized Recording of Symptoms and Trigger Factors

This part of the intervention was delivered via a specifically modified version of the publicly available app “NIA” (Nia Health GmbH). In the project-specific app version (not publicly available), ADCompanion offers content from the corresponding patient educational curricula of the “Arbeitsgemeinschaft Neurodermitisschulung” (AGNES, German Working Group on Atopic Dermatitis Training for Children) [11] and “Arbeitsgemeinschaft Neurodermitisschulung für Erwachsene” (ARNE, German Working Group on Atopic Dermatitis Training for Adults) [12], which have been edited in cooperation with teams of experts to adapt them for digital and remote communication. Prepared texts, expert interviews, and video tutorials convey specialist knowledge in easy-to-understand language and clarify common questions from those affected. The project app also enables the standardized recording of “skin mood” (dryness, oozing/crusting, redness, scratching, swelling, and skin thickening) via the validated Patient-Oriented Scoring Atopic Dermatitis Index (PO-SCORAD) [28]. In addition, possible trigger factors can be recorded and skin conditions documented using photos. Individual reports can be downloaded in a .pdf format and shared with the attending health care professionals. For screenshots of the study app, please see Figure 2. Use of the digital intervention was intentionally not restricted or prescribed in order to assess real-world utilization. Participants in the intervention group received full access to all app components and were free to decide how often and which elements to use. No minimum number of logins, completed modules, or counseling sessions was defined to constitute intervention adherence.

**Figure 2. F2:**
[figure not shown]
Screenshots of the study app including video and text material from the AGNES training curriculum. AGNES: Arbeitsgemeinschaft Neurodermitisschulung e.V. (German Working Group on Atopic Dermatitis Training for Children).

#### Needs-Based, Qualified Nutritional Advice via a Digital Consultation Platform

As AD is often associated with sensitization to various foods, especially in childhood, uncertainties regarding the correct diet are common and malnutrition can occur. To counteract this risk and support the adequate implementation of an elimination diet, ADCompanion offers the option of qualified nutritional therapy advice via video.

#### Individual Video Care Advice via Digital Consultation Platform

The needs-adapted skin care advice by specifically qualified nurses (AGNES trainer certification) is provided in accordance with the validated care advice initiative of AGNES e.V. [29].

#### Individual, Psychosocial Counseling on Dealing With the Disease and Possible Coping Strategies

AD patients of all age groups and their caregivers/families often face major challenges, particularly due to the pronounced itching, but also cosmetic aspects and restrictions in everyday life, work, and sleep. ADCompanion offers the possibility of needs-adapted support by means of video counseling by specifically qualified psychologists (AGNES trainer certification).

### Primary Hypothesis

Patients in the intervention group have a comparable or lower severity of AD, as measured by doctor-assessed SCORAD [30], than patients in the control group 6 months after the start of intervention (noninferiority).

### Primary Outcome

The primary outcome of the study is the change in physician-assessed SCORAD index [31] 6 months after baseline. SCORAD is a validated composite instrument combining the extent of affected skin areas, the intensity of 6 clinical signs, and patient-reported symptoms (pruritus and sleep loss), resulting in a total score ranging from 0 to 103, with higher scores indicating more severe disease.

### Secondary Outcomes

Secondary outcomes capture patient- and caregiver-reported disease severity, symptoms, quality of life, psychosocial burden, family impact, and digital health literacy. Subjective disease severity is assessed using the PO-SCORAD [28], a self-assessment version of SCORAD aligned with the clinician-rated instrument. In addition, clinician-rated disease severity is measured using the Eczema Area and Severity Index (EASI) [31], which evaluates the extent and intensity of eczema lesions across 4 body regions and yields a total score ranging from 0 to 72.

Dermatology-specific symptom burden and quality of life are assessed using the German version of the SKINDEX-29 (29-Item Dermatology-Specific Quality of Life Questionnaire) [32], which includes symptom, emotional, and functional domains scored on a 0‐100 scale, with higher scores reflecting greater impairment. Itch-related cognitions and coping strategies are assessed using age-appropriate validated German instruments, namely JUCKKI/JUCKJU (Itch Questionnaire for Children/Itch Questionnaire for Adolescents) for itch-related cognitions and COPEKI/COPEJU (Coping With Disease Questionnaire for Children/Coping With Disease Questionnaire for Adolescents) for coping with itch and disease-related stress [33].

For infants and toddlers, health-related quality of life is assessed using the Infants’ Dermatitis Quality of Life Index (IDQoL) [34], a parent-reported questionnaire with total scores ranging from 0 to 30. The impact and burden of AD on family life is measured using the Familien-Belastungs-Fragebogen (FaBel) [35].

Digital health literacy is assessed using the eHealth Literacy Scale (eHEALS) [36], an 8-item self-report questionnaire with total scores ranging from 8 to 40, where higher scores indicate higher perceived competence in accessing and using digital health information.

Further secondary outcomes are the number of responders (SCORAD improvement of more than ≥8.7 points at 6 and 12 months compared to baseline [37]) and the association between the use of individual care components by patients and/or caregivers and the individual level of competence in dealing with digital health services/information (eHEALS questionnaire on digital health literacy, measured at baseline [27]).

All outcome measures, including assessment timepoints and target populations, are summarized in Table 1. Clinician-rated outcomes are assessed during study visits by trained study personnel, while patient- and caregiver-reported outcomes are collected electronically.

**Table 1. T1:** Overview of tools and timepoints of data collection.

Variable	Timepoint of recording			
	Baseline (T0)	Weekly recording via study app	6 months after baseline (T1)	12 months after baseline (T2)
Primary outcome				
SCORAD^a^	✓		✓	
Secondary outcome				
SCORAD	✓			✓
EASI^b^	✓		✓	✓
PO-SCORAD^c^	✓	✓	✓	✓
SKINDEX-29^d^	✓		✓	✓
IDQOL^e^	✓		✓	✓
Impact on Family Scale	✓		✓	✓
JUCKKI^f^/JUCKJU^g^	✓		✓	✓
COPEKI^h^/COPEJU^i^	✓		✓	✓
eHEALS^j^	✓			
Medication diary	✓	✓	✓	✓
Questionnaire on the use of medical services	✓		✓	✓

a SCORAD: Scoring Atopic Dermatitis Index.

b EASI: Eczema Area and Severity Index.

c PO-SCORAD: Patient-Oriented Scoring Atopic Dermatitis Index.

d SKINDEX-29: 29-Item Dermatology-Specific Quality of Life Questionnaire.

e IDQOL: Infant’s Dermatology Quality of Life Index.

f JUCKKI: Itch Questionnaire for Children.

g JUCKJU: Itch Questionnaire for Adolescents.

h COPEKI: Coping With Disease Questionnaire for Children.

i COPEJU: Coping With Disease Questionnaire for Adolescents.

j eHEALS: eHealth Literacy Scale.

### Statistical Analysis

#### Analysis of Primary Outcomes

The statistical analysis of the main hypothesis of noninferiority will be performed using analysis of covariance (ANCOVA). This analysis framework also enables the evaluation of potential superiority if supported by the data. The primary outcome is the disease severity measured via change in SCORAD 6 months after study inclusion. Covariates are SCORAD at baseline and patient age. Center heterogeneity is accounted for by random intercepts using linear mixed models. Noninferiority for the overall study population is considered proven if the 95% CI of the mean group differences between the control and intervention groups determined by ANCOVA (linear mixed model) is less than 4 points in favor of the standard therapy. Once noninferiority has been demonstrated in the overall group, noninferiority is demonstrated in the individual age strata. For this purpose, the regression model is extended by an interaction term for the age groups and the allocation (intervention vs control). Based on marginal estimators, the 95% CIs for the group differences (intervention vs control) are then determined for the respective age strata. Noninferiority in the individual age strata is shown following the principle of hierarchical testing [38] using a family-wise error rate of 0.025 (one-sided) and applying the Bonferroni and Holm method [39] for the adjustment for multiple testing if (1) in the stratum with the strongest effect, the 98.3% (family-wise error rate of 0.025/3) CI of the marginal estimator for the group difference in the SCORAD is less than 4 points in favor of the standard treatment; (2) in the stratum with the second strongest effect, the 97.5% (family-wise error rate of 0.025/2) CI of the marginal estimator for the group difference in the SCORAD is less than 4 points in favor of the standard treatment; and (3) in the stratum with the smallest effect, the 95% (family-wise error rate of 0.025) CI of the marginal estimator for the group difference in the SCORAD is less than 4 points in favor of the standard treatment.

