### Study Design

ADCompanion is a prospective, multicenter, 1:1 randomized 2-arm intervention study with a noninferiority design. Patient enrollment is stratified in 3 age groups: infants, toddlers, and preschool children (age 3 months to 6 years); school children and adolescents (age 7‐17 years); and adults (age 18‐65 years). The need for this stratification results from known differences in care between age groups and a high spontaneous remission rate in preschool age.

The study groups differ as follows: The control group receives standard therapy (optionally including access to face-to-face training in small groups where possible, in line with routine care) and access to a limited version of the study app containing standardized symptom and trigger recording only. Routine care in this trial reflects routine real-world care as delivered across participating centers and does not mandate participation in structured face-to-face education programs. The intervention group receives standard medical therapy without access to face-to-face group training, but with full use of the app, including online training content and optional individual counseling via video in the areas of care, nutrition, and psychosocial support. Participants can freely decide which counseling sessions they want to book. Per specialist area, a maximum of 3 sessions can be booked during the first monitoring period (6 months). For an overview on the study visits and timeline, please see Figure 1. Due to the nature of the intervention, blinding of participants or investigators was not feasible and therefore not applied.

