#### Sample Size Calculation

The case number estimate was based on a noninferiority design and the primary endpoint SCORAD 6 months after baseline. The noninferiority margin was set at 4 points, as differences in SCORAD of 4 points or less are not considered clinically relevant [19]. Using a *t* test for independent samples with a power of 85% and a 1-sided significance level of 0.025, noninferiority of ADCompanion compared to standard therapy can be demonstrated, assuming a common SD of 15 points (from Staab et al [11] and Heratizadeh et al [12], a common (pooled) SD of 11.2 was calculated). Considering possible stronger variances in our study design, the power calculation was based on a common SD of 15 points if 254 patients per group are included. This corresponds to a total number of cases of 508 patients. Based on an expected dropout rate of about 15%, 600 patients should be included in the study (corresponding to a dropout rate of 15.3%). This case number estimation was performed with nQuery Advisor 8 (nQuery 2017 Sample Size and Power Calculation, “Statsols,” Statistical Solutions Ltd).

We assume that the intervention effects may be different in the various age groups. Since the spontaneous remission rates are much higher in younger children in particular, lower effect sizes are to be expected compared to older children and adults. Therefore, proportionally more patients should be recruited in the age group under 7 years. Staab et al [11] determined different effect sizes (Cohen *d*) in different age groups: 3 months to 7 years: 0.23; 8‐12 years: 0.35; 13‐18 years: 0.76. Due to the expected different effect sizes, age group–specific recruitment was determined as (1) age 3 months to 6 years: n=260 (130 IG + 130 CG); (2) age 7‐17 years: n=140 (70 IG + 70 CG); and (3) 18‐65 years: n=200 (100 IG + 100 CG), where CG represents the control group and IG represents the intervention group.

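### The confirmatory age-stratum intervals hold their stated error rate only if the residual SD is the same in all three age groups, which the protocol neither states nor supports

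*Protocol article*

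**What the plan says.** The section Analysis of Primary Outcomes names an ANCOVA fitted as a linear mixed model, with baseline SCORAD and age as covariates and a random intercept for center. Once overall noninferiority is shown, this model is extended by an interaction between age group and allocation, and "Based on marginal estimators, the 95% CIs for the group differences (intervention vs control) are then determined for the respective age strata". The strata are then tested "using a family-wise error rate of 0.025 (one-sided) and applying the Bonferroni and Holm method", with intervals of 98.3%, 97.5% and 95% for the strata ranked by effect. Each is compared with the 4-point margin. The text does not mention residual variance, either common or by stratum.

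The Sample Size Calculation section gives one SD for the whole trial: "the power calculation was based on a common SD of 15 points if 254 patients per group are included". It reports 11.2 as the SD pooled from two earlier education trials and explains the increase to 15 with the words "Considering possible stronger variances in our study design". No SD by age group is given.

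**The concern.** An interaction term lets each age group have its own treatment difference. It does not let each group have its own spread. If the model has one residual variance, every stratum interval is built from an average SD over all ages. The interval is then too narrow in a stratum whose SD is above average and too wide in one whose SD is below average.

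The stratum intervals are not descriptive. They decide three noninferiority claims under a stated family-wise error of 0.025, and the Holm procedure controls that error only if each single test holds its own level. At stake are a false claim of noninferiority in one age group and a missed one in another, both from the same fit.

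**Working it through.** **The plan's own figure first.** Inputs from Sample Size Calculation: "The noninferiority margin was set at 4 points", SD 15, true difference 0, "with a power of 85% and a 1-sided significance level of 0.025". The normal approximation gives n = 2 × (1.960 + 1.036)² × 15² / 4² = 252.5, so 253 per group. The noncentral t test gives power 84.93% at 253 and 85.07% at 254, so 254 per group is right. 1 − 508/600 = 15.3%, as stated. The overall sample size is not in question.

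**Evaluable numbers per arm.** Planned 130, 70 and 100 per arm, times 508/600, gives about 110, 59 and 85.

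**Stratum SDs (assumption).** They are kept within the article's two values, 11.2 and 15, as stand-ins for the residual SD after covariate adjustment.

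**Formula for one stratum.** An interval built on the pooled SD has a true one-sided error of 1 − Φ(z × SD_pooled / SD_stratum), with z = 1.96 at the 0.025 step.

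**Example: ages 7-17 at 15, the other two groups at 11.2.**
- SD_pooled = √[(110 × 11.2² + 59 × 15² + 85 × 11.2²) / 254] = √(37,736 / 254) = 12.19.
- Ages 7-17: 1.96 × 12.19 / 15 = 1.593, error 5.6% instead of 2.5%. At the 0.025/3 step it is 2.6% instead of 0.83%. The 95% half-width is 4.39 points, against 5.40 with the stratum's own SD.
- Other two strata: 1.96 × 12.19 / 11.2 = 2.133, error 1.6%.

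**Other assignments within the same range (nominal 2.5%).**

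| SDs (3 months-6 y / 7-17 y / adults) | Error of each stratum interval taken alone |
|---|---|
| all equal | 2.5% / 2.5% / 2.5% |
| 11.2 / 15 / 15 | 0.9% / 3.9% / 3.9% |
| 15 / 11.2 / 11.2 | 4.5% / 1.2% / 1.2% |
| 15 / 11.2 / 15 | 3.2% / 0.65% / 3.2% |
| 11.2 / 15 / 11.2 | 1.6% / 5.6% / 1.6% |

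**The procedure as planned.** The figures above take one interval alone. The protocol first requires overall noninferiority and then the three Holm steps. I simulated that sequence 400,000 times per scenario: normal outcomes, estimated variances, no center effect or covariates, SDs 11.2/15/11.2, and ages 7-17 truly 4 points worse. Ranges cover ranking the strata by effect, as the protocol says, and by p value.

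| True difference in the other two strata | Family-wise error, pooled variance | Family-wise error, stratum variances |
|---|---|---|
| 4 points in favour of the intervention | 5.4-5.5% | 2.3-2.5% |
| zero | 3.1-3.7% | 0.9-1.6% |
| 4 points worse | 0.9% | 0.7-0.8% |

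With SD 15 in every stratum, the first row becomes 2.1-2.3% with either method.

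**Power in the example at zero true difference, 95% step alone.** Power is Φ(4/SE − 1.96 × SD_pooled / SD_stratum) with pooled variance and Φ(4/SE − 1.96) with the stratum's own.
- Ages 7-17: SE = 15 × √(2/59.3) = 2.755. Φ(1.452 − 1.593) = 44% pooled, Φ(1.452 − 1.96) = 31% with its own SD.
- Youngest stratum: SE = 11.2 × √(2/110.1) = 1.510. Φ(2.650 − 2.133) = 70% pooled, Φ(2.650 − 1.96) = 75% with its own SD.

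**The case against.** The strongest objection is that the assumption criticised is not written down. A single residual variance is inferred from the ordinary form of the model, and a journal article may leave residual structure or robust standard errors to the analysis plan. The article says that plan is finalized, and it is not shown. This stands: there is no error or contradiction in the text, and the plan may already deal with the point.

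A reader might infer that the protocol itself expects unequal variances. It does not. The Study Design section bases the age stratification on "known differences in care between age groups and a high spontaneous remission rate in preschool age", and the sample size section adds "Since the spontaneous remission rates are much higher in younger children in particular, lower effect sizes are to be expected". These statements concern course and treatment effect, and the interaction term handles differing effects. The remark about stronger variances compares the whole trial with earlier studies. Higher remission could change the spread, but the direction is open: scores near the floor would reduce it, and a mixture of remitters and non-remitters would raise it.

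A reader might also take the single-interval percentages as the error of the planned procedure. They are not. The overall test gives real protection, and the family-wise error clearly exceeds 2.5% only under a mixed truth, in which the stratum with the larger SD is worse while the others are equal or better. That truth cannot be dismissed, since the protocol itself assumes that effects may differ by age. The overall test and the Holm steps therefore reduce the problem without removing it.

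**Conclusion.** The point holds in limited form. The stated 0.025 for the stratum claims depends on equal residual SDs across age groups, and the article gives no support for that. Within its own SD range, the worst case is a family-wise error of about 5.5%, roughly double the stated level. It falls to about 3-4% when the other strata show no difference and below 1% when all strata are 4 points worse. With equal SDs the effect is nil.

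These sizes rest on assumed stratum SDs, the planned stratum sizes after 15.3% dropout, and a model without center or covariate effects. The documents do not support saying that the intervals are wrong, only that their validity rests on an unstated condition. The overall primary test is little affected, because allocation is 1:1 and balanced on age, and the sample size stands. Severity is low.

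**What to change.** Unless the analysis plan already does so, fit the interaction model with a residual variance that may differ by age group, or with heteroscedasticity-robust standard errors. Take the 98.3%, 97.5% and 95% stratum intervals from that fit, and state the variance assumption in one sentence. Leave the overall primary test unchanged. The Results section reports the data analysis as complete, so an analysis added now should be labelled as added and shown beside the planned one, with the observed SD in each age group.

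The cost is one model option and one sentence, plus a negligible loss of degrees of freedom if the SDs are equal. The real downside is a wider interval and lower power in any stratum whose SD is above average. In the worked example, ages 7-17 fall from 44% to 31% at the 95% step, and the higher figure was obtained at an error of 5.6% rather than 2.5%.

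### The age-stratum step-down names Holm but orders strata by estimated effect, not p-value; with unequal strata this costs a modest amount of power, not error control

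*Protocol article*

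**What the plan says.** The rule is in the protocol article under *Analysis of Primary Outcomes*. The strata are reached only through a gate: "Once noninferiority has been demonstrated in the overall group". They are then tested "following the principle of hierarchical testing", "using a family-wise error rate of 0.025 (one-sided) and applying the Bonferroni and Holm method [39] for the adjustment for multiple testing".

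Three conditions follow, each tied to a rank of the estimated effect:

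1. "in the stratum with the strongest effect, the 98.3% (family-wise error rate of 0.025/3) CI of the marginal estimator for the group difference" must lie within the 4-point margin;
2. "in the stratum with the second strongest effect, the 97.5% (family-wise error rate of 0.025/2) CI of the marginal estimator", same margin;
3. "in the stratum with the smallest effect, the 95% (family-wise error rate of 0.025) CI of the marginal estimator", same margin.

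No step refers to a p-value, and no sentence says what happens after a failed step.

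*Sample Size Calculation* fixes unequal strata: 260 patients aged 3 months to 6 years, 140 aged 7–17 and 200 aged 18–65, each split 1:1. The youngest group was enlarged deliberately because smaller effects were expected there.

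**The concern.** Holm's procedure tests the hypothesis with the smallest p-value first, at the strictest level. The article borrows Holm's levels but ranks by size of effect. The two rankings must coincide only if all strata are estimated with equal precision, and here they are not.

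A small stratum can show the largest estimate and still have too wide an interval to pass at 98.3%. If testing ends there, a larger stratum with stronger evidence is never examined. Two analysts, one applying the named method and one applying the three listed steps, could then report different age groups as noninferior from the same data.

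**Working it through.** **Inputs.** Margin 4; one-sided family-wise level 0.025; SD 15 (planning) and 11.2 (pooled from the two earlier education trials); 254 per group after dropout from 600 recruited; strata 260/140/200. All are in *Sample Size Calculation* and *Analysis of Primary Outcomes*.

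**1. The plan's own figures reproduce.** n = 2(1.960 + 1.036)² × 15² / 4² ≈ 252.5, so 253 per group by normal approximation; the noncentral t gives 254 (power 85.07%). Dropout: 1 − 508/600 = 15.3%. Interval levels 1 − 2 × 0.025/k for k = 3, 2, 1 give 98.3%, 97.5% and 95%. These are exactly Holm's levels; only the ordering departs.

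**2. Precision by stratum.** With a common SD and equal dropout, completers per arm are 130, 70 and 100 times 508/600, about 110, 59 and 85. SE = SD × √(2/n).

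| Stratum | SE, SD 15 | SE, SD 11.2 |
|---|---|---|
| 3 months–6 y | 2.02 | 1.51 |
| 7–17 y | 2.76 | 2.06 |
| 18–65 y | 2.31 | 1.72 |

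The ratio of the middle to the youngest stratum is √(110/59) = 1.365, about 37% larger (1.363 from the unrounded planned sizes).

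**3. When the orders differ.** The p-value depends on (4 − estimate)/SE, so the ranking by p equals the ranking by estimate only when the SEs are equal. To pass in first position (z = 2.394), a stratum needs an estimate below 4 − 2.394 × SE. At SD 11.2 that is +0.4 for the youngest and −0.9 for 7–17; at SD 15, −0.8 and −2.6 (positive values favour control).

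**4. A worked case (SD 11.2).** Estimates −0.2 / −0.8 / 0.0 (youngest / 7–17 / adults). The overall estimate is −0.27 with upper 95% limit 1.67, so the gate is passed.

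- One-sided noninferiority p-values: 0.0027 / 0.0098 / 0.0101.
- As written: 7–17 comes first. Its 98.3% upper limit is −0.8 + 2.394 × 2.057 = 4.13, above 4. With stopping, no stratum is claimed.
- Holm: 0.0027 ≤ 0.0083, 0.0098 ≤ 0.0125 and 0.0101 ≤ 0.025. All three are claimed.

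**5. Direction of the difference.** Suppose m strata pass in effect order. The level rises at each step, so their p-values, once sorted, also meet Holm's levels, and any stratum with a smaller p-value passes too. Every stratum claimed as written is therefore also claimed by Holm.

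**6. Error control.** With stopping at the first failure, at the first false claim the level is 0.025/(strata not yet claimed). That is at most 0.025 divided by the number of strata that are truly not noninferior, so the Bonferroni bound gives 0.025 whatever the ordering. In the null scenarios simulated, the largest family-wise error for effect ordering was 0.0247.

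**7. Size, by simulation.** Normal independent stratum estimates, overall gate applied, stopping at the first failure, at least 400,000 trials per scenario. No true difference:

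| | SD 11.2, as written | SD 11.2, Holm | SD 15, as written | SD 15, Holm |
|---|---|---|---|---|
| Youngest stratum claimed | 60.9% | 65.8% | 32.9% | 36.2% |
| At least one stratum claimed | 82.2% | 85.6% | 54.9% | 57.9% |

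Repeat runs agree within about 0.2 percentage points. A different stratum comes first in 21% (SD 11.2) or 17% (SD 15) of trials. Holm claims at least one further stratum in 5.7% or 3.9%. Across true differences from 0 to −2 that share runs from 1.6% to 5.7%. With the recruited sizes in *Results* (252/146/205) and the control arm's loss (233 of 300 completed, 22.3%) assumed in both arms, it is 4.5% (SD 11.2) or 2.8% (SD 15) at zero difference. Effect ordering never claimed a stratum that Holm did not.

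**The case against.** The best defence is that the article names Holm and uses its exact levels, so the references to effect may be shorthand for strength of evidence in a condensed text, with the ordering set correctly in the analysis plan. That is possible and cannot be excluded. But the article does not merely leave the ordering open: it states one, three times, and the stated one is not Holm's.

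The stop rule is also an inference. It rests on the references to hierarchical testing and to Holm; no sentence spells it out. The blocking described here depends on it.

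Several stronger readings are tempting and are not supported:

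- **That error is inflated or the primary result compromised.** Neither holds. With stopping, family-wise error is controlled under both orders, and the overall test precedes the strata and is untouched.
- **That the small stratum often blocks the others.** At zero true difference, 7–17 comes first in about 36% of trials, against 33.3% for equal strata. It comes first, fails and wipes out claims Holm would have made in about 3% (3.1% at SD 11.2, 2.6% at SD 15).
- **That these are the only confirmatory claims below the overall result.** The text does not say so; *Analysis of Secondary Hypotheses* also describes tests.
- **That changing the rule is free.** The Abstract reports a finalised analysis plan and *Results* reports completed analysis. Moving now to a rule that can only add claims would be a post hoc change.

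**Conclusion.** The point stands as an internal inconsistency with a small cost in power. Read literally, the step-down is valid but dominated: p-value ordering has the same error control and never claims less. The cost is at least one lost stratum claim in about 2–6% of trials, and some 3 to 5 percentage points of power for the youngest stratum when there is no true difference.

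This rests on a common SD across strata, equal dropout by stratum, normal estimates, no variance reduction from covariates, and stopping at the first failure. Whether the actual analysis departs from Holm is not established, because the analysis plan is not shown.

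**What to change.** **Wording.** Replace the ranking by strongest, second strongest and smallest effect with a ranking by smallest, second smallest and largest one-sided noninferiority p-value (equivalently, descending (4 − estimate)/SE). Keep 0.025/3, 0.025/2 and 0.025. Add one sentence saying that testing stops at the first stratum that fails.

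**Handling, given the trial's stage.** First state which ordering the finalised analysis plan prespecified.

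- If it is p-value ordering, correct the article.
- If it is effect ordering, keep that as the prespecified result and report the Holm result beside it, labelled as a post hoc change.

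**Cost.** The rewording takes a sentence or two and needs no new data. The real cost is credibility: an unexplained switch after analysis would look driven by the data, so the prespecified rule has to be disclosed either way.
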